### Hemostatic Devices and Self-Adhesive Torniquet Wrap

The MCD that will be utilized in the RAPHE study has been in clinical use for more than 15 years, with established results (22). It features a single-use, transparent, purpose designed inflatable pneumatic airbladder (18 ml in volume) and a positioning marker for optimal placement at the junction of the introducer and intact skin. This MCD is held in place by a hook-and-loop fastener. Inflation of the device is achieved through a valve equipped line, using a custom made 20 ml syringe. This syringe allows for easy titration (0.5 ml increments) of air quantity within the pouch, allowing for effective PH measures. This MCD comes in two sizes (24 cm regular and 29 cm large) to accommodate for variable wrist sizes. It is used in catherization laboratories all over the world and thus makes for an excellent gold-standard device and as such the control MCD in the RAPHE study.

The first bioactive hemostatic device that will be investigated in study is a 100% chitosan sponge dressing. Chitosan is linear polysaccharide composed of randomly distributed deacetylated and acetylated D-glucosamine/N-acetyl-D-glucosamine units. It is produced from shells of shrimp and other crustaceans following alkaline treatment. It is a non-toxic, environmentally friendly substance with a variety of uses including agriculture, food supplementation and industrial applications. The one notable hindrance of the substance is potential allergic reactions, that although rare are known to manifest and thus inhibit its use in sensitive individuals. Chitosan may be formed and cut to any required shape and size. From a medical point of view, chitosan was first used in military practice, aiding bleeding control during battlefield operations (23). Civilian use was gradually introduced in the following years. The mechanism of action of chitosan is based on an electrical polarity difference between the positive charged seal and the negatively charged blood forming a strong mechanical barrier. Applying pressure to chitosan on a bleeding wound thus leads to rapid thrombocyte aggregation and thrombus formation. The RAPHE study will utilize a 3.5 × 3.5 cm sterile 100% chitosan sponge dressing that has been specifically developed to handle hemostasis of the radial and comparable size arteries.

The second bioactive device to be investigated will be a purpose designed topical disc containing potassium-ferrate powder and a hydrophilic agent as dual active ingredients. Potassium-ferrate is chemical compound with the formula K_2_FeO_4_. It is a highly reactive substance, that when encountering water, rapidly decomposes into ferric oxide (Fe_2_O_3_). The released cationic iron rapidly activates thrombocytes and initializes the coagulation cascade that leads to rapid thrombus formation. First medical application of this dual compound was in a powder form used to ease seeping hemorrhages around large bore catheter insertion sites. Eventually the technology evolved into a tailored disc containing a mix of compressed potassium-ferrate powder and a bioactive hydrophilic agent. This topical disc, when placed on a bleeding wound engages the hydrophilic active seal and desiccates the surrounding blood. As cationic-protonic exchange of potassium-ferrate decomposition takes place local pH levels are pushed to a highly acidic value, thereby again increasing blood desiccation. This process completes a strong hermetic seal.

Appropriate, quick, and effective fixation of the chitosan sponge dressing and potassium-ferrate discs are crucial for continues hemostasis control. We will be using the self-adherent elastic wraps to hold the bioactive devices in place. These do not require any further adhesives, pins, or clips to fixate and only bind to themselves. Using these novel wraps ensures excellent gripping of hemostatic devices and allow for fast un- and re-wrapping.

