### Patient Enrollment, Inclusion/Exclusion Criteria

For potential enrollment in the RAPHE trial subjects must have a clinical indication for a radial approach coronary angiography and be between ages of 18 and 85 years. The use of standard 5, 6, or 7 French introducer sheaths will be required during the trial. A pre-screening sonographic evaluation of the radial artery will also be required to measure the diameter of the vessel. A minimum diameter of 1.8 mm-s is needed for potential enrollment. If a radial artery diameter of < 1.8 mm-s is detected, patients will discontinue the study as an early screen failure. Late screen-fail will occur if any other form of arterial puncture is needed during the procedure apart from the initial one, albeit upgrading the introducer size to a larger one will be allowed.

Exclusion criteria firstly focus on safety, thus potential patients shall be excluded based on the following: highly advanced age (>85 years) (I), sudden cardiac death and successful resuscitation prior to the index angiogram (II), unstable circulation prior to the index angiogram (III), pregnant or nursing (IV). Furthermore, three clinical exclusion criteria have been laid down, factors that are known to cause increased puncture site complications, to ensure no distortion of the collected data. These are: unusually small diameter of the radial artery (< 1.8 mm) (V), known and treated systemic autoimmune disease, e.g., rheumatoid arthritis, systemic lupus erythematosus etc. (VI) and severe, peripheral arterial vasculitis/disease, e.g., Buerger’s disease, Takayasu’s arteritis etc., (VII).

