### Randomization Procedure

Randomization of consented subjects may only take place in the absence of exclusion criteria after removal of the last coronary catheter, by a physician participating in the study. It will take place in a 1:1:1 ratio, independently for every site via a computer algorithm, between the: pneumatic balloon MCD, potassium-ferrate disc and 100% chitosan sponge devices.

The pneumatic balloon based MCD serving as the control device will be placed on the introducer sheath inflated with the provided syringe to 12 ml-s with simultaneous removal of the introducer. An additional 2 ml-s of air will be inflated in case of acute bleeding and repeated if needed. It will be removed via a simplified patent hemostasis protocol (24), in which, after achieving primary hemostasis, exact titration to true PH we will be achieved by removing 2–3 ml-s of air every 10–15 min using a pulse oximeter to verify patency. At 0 ml-s of remaining air the device will be removed. These procedures will be carried out by qualified nursing staff. Nurses have been instructed to strictly adhere to the PH protocols and to contact study physicians in case of any potential adverse events, especially those in conjunction with radial hemostasis.

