The standalone potassium ferrate disc and chitosan sponge devices will both be used in a similar way. They will be placed onto the junction of the intact skin and introducer and manually compressed. To aid better initial compression and prevent device adhesion to bloody surgical gloves, a ball gauze will be placed on the chitosan device. The potassium-ferrate disc will be compressed alone. During compression the introducer will be removed, allowing for a visible amount of blood to appear, which will activate the hemostatic properties in both devices. Strong manual compression will be held for 1 min. Devices will then be banded and held in place using self-adherent wraps as detailed above. Strong, occlusive fixation of the devices will be upheld for a total of 10 min, after which the self-adherent bond will be fully unwrapped until the hemostasis device is visible. By this time both devices will have activated and initiated the coagulation cascade and are firmly attached to the puncture site. If acute bleeding occurs, an additional, minimum 5 minutes of compression will be applied. If initial devices are no longer fit for use, a new similar one will be used. Re-wrapping will then occur without the application of relevant pressure, in a non-occlusive way. During this time the wrapping will only protect the hemostasis device from external influence (e.g., accidental dislodgement, slipping etc.). If the second randomized study device also fails to contain puncture site bleeding a bail-out device of choice shall be applied as per protocol, the choice of which is left to the discretion of the attending physician. After a period of 120 ± 15 min the self-adherent wrapping will be removed. The chitosan sponge device will also be removed using sterile saline irrigation. The potassium-ferrate disc will remain in place and removed by the patient after 24 hours post-procedure.

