### Flowchart

[figure not shown]

The above flowchart details the RAPHE trial algorithm of subject inclusion/exclusion, allocation, randomization, and clinical procedures. Specifics of all three arms are displayed along with the required post-operative and follow-up measures.

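### The article says chitosan is unsuitable for sensitive patients, but none of its seven numbered exclusions covers known chitosan hypersensitivity

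*Protocol article*

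**What the plan says.** Three parts of the protocol article bear on this.

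- **Hemostatic Devices and Self-Adhesive Torniquet Wrap.** The article describes the origin of chitosan ("It is produced from shells of shrimp and other crustaceans following alkaline treatment") and then gives its single noted drawback: "potential allergic reactions, that although rare are known to manifest and thus inhibit its use in sensitive individuals".
- **Patient Enrollment, Inclusion/Exclusion Criteria.** The list opens with "Exclusion criteria firstly focus on safety, thus potential patients shall be excluded based on the following" and gives items (I) to (IV). It continues with "Furthermore, three clinical exclusion criteria have been laid down", which are items (V) to (VII). None of the seven mentions allergy.
- **Randomization Procedure.** Entry is controlled by that list: "Randomization of consented subjects may only take place in the absence of exclusion criteria after removal of the last coronary catheter". Allocation is then 1:1:1 between the pneumatic band, the potassium-ferrate disc and the chitosan sponge. The route to a non-randomised device is also given: "If the second randomized study device also fails to contain puncture site bleeding a bail-out device of choice shall be applied as per protocol".

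**The concern.** The article identifies a group of patients for whom one of its three study devices is unsuitable, but the eligibility rules do not keep that group out. Following the printed list exactly, a site could enrol a patient with a recorded chitosan sensitivity, randomise that patient, and be assigned the sponge.

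What is at stake is participant safety and agreement between two parts of one document. Adverse events are collected at both follow-up visits, so a reaction would be recorded, but recording does not prevent it.

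Timing adds to the problem. Randomisation comes after the last coronary catheter is out. If the sensitivity first comes to light then, staff must either expose the patient or depart from the allocation, and under the planned intention-to-treat analysis that patient still counts in the chitosan arm. Asking before the procedure avoids both.

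**Working it through.** There is no stated figure to reproduce. The check compares the sections of the article with each other and adds simple arithmetic.

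**Step 1: the exclusions, one by one** (Patient Enrollment, Inclusion/Exclusion Criteria)

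| Item | Content | Covers chitosan sensitivity? |
|---|---|---|
| I | Age over 85 | No |
| II | Resuscitated sudden cardiac death | No |
| III | Unstable circulation | No |
| IV | Pregnancy or nursing | No |
| V | Radial artery under 1.8 mm | No |
| VI | Treated systemic autoimmune disease | No; its examples are rheumatoid arthritis and lupus |
| VII | Severe peripheral vasculitis or arterial disease | No |

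Count: 4 safety items + 3 clinical items = 7. Items naming allergy or hypersensitivity = 0.

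**Step 2: is the gap closed elsewhere in the visible text?**

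- *Inclusion criteria:* a clinical indication for radial angiography, age 18 to 85, sheath size and vessel diameter. Nothing on allergy.
- *Patient Data Collection:* the history items are itemised and allergy is not among them.
- *Endpoint Definitions and Hypothesis* and *Randomization Procedure:* a second identical device, and then a bail-out device, follow only from bleeding or from a device that can no longer be used. Sensitivity is not a trigger.
- *Sonographic Evaluation and Follow-up:* adverse events are collected after exposure.
- *Safety and Termination:* the interim review concerns comparisons between devices, not individual eligibility.

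None of these supplies a rule.

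**Step 3: chance of allocation.** With 600 patients at 1:1:1, each arm has 600 / 3 = 200. A sensitive patient who meets the printed criteria has a chance of 200 / 600 = 1/3 of being assigned chitosan.

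**Step 4: planned contact time.** The sponge comes off with the wrap at 120 ± 15 minutes:

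- shortest: 120 − 15 = 105 minutes
- longest: 120 + 15 = 135 minutes

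The text does not say whether this clock starts at application or at re-wrapping. If it starts at re-wrapping, the 1 minute of manual pressure and 10 minutes of firm fixation come on top, giving 105 + 11 = 116 to 135 + 11 = 146 minutes. Either way contact lasts roughly two hours.

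**Step 5: number affected.** If a proportion *p* of enrolled patients had known sensitivity, the expected number given the sponge would be 200 × *p*. The article gives no value for *p* and says only that reactions are rare, so no case count is claimed.

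**The case against.** The strongest reply is that this is a journal article and condenses a longer protocol. Contraindications to a device's own material often sit in the full protocol, the instructions for use or the investigator file, and none of these is shown. The sentence on allergy is general background on the substance, and it shows that the authors know of the limitation. Only the second group of exclusions is given a count, so the list as a whole is not expressly declared exhaustive. The flowchart, of which the article says "The above flowchart details the RAPHE trial algorithm of subject inclusion/exclusion", is not available in the copy reviewed and might contain the rule. A sensible physician would also decline to enrol such a patient.

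Much of this limits the claim. The full protocol or the flowchart may already deal with the matter, and clinical judgement will often prevent harm. It is also fair that the article does not say patients with shellfish allergy react to chitosan, so a crustacean exclusion does not follow from its text.

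The inconsistency in print remains. The article did not leave eligibility to another document. It printed a numbered list, began that list with safety, and made it the condition for randomisation. A list followed as written should not admit patients for whom the same article says a study device is unsuitable. If the full protocol already has the exclusion, the published list is incomplete and needs only a correction.

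**Conclusion.** The point holds as a low-severity safety and consistency issue. None of the seven listed exclusions covers hypersensitivity, and a patient with known chitosan sensitivity who meets the printed criteria has a 1/3 chance of about two hours' contact with the material.

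The consequence for the trial's results is negligible. Allergy is not a component of the primary composite, reactions are described as rare, and neither the sample size nor the analysis depends on it. The number of patients affected is unknown and probably small.

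The conclusion rests on the visible text alone, without the flowchart or the full protocol, and it concerns sensitivity already known before enrolment. Confidence is therefore medium.

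**What to change.** Add known hypersensitivity to chitosan as item (VIII) of the exclusion list, applied before randomisation and to all three arms so that the groups stay comparable. Ask about it at pre-screening, before the procedure. The investigators should decide whether to extend the wording to crustacean allergy or to materials in the other study devices, since the article does not settle either. If the full protocol already has such a rule, bring the published list into line with it.

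The cost is one line in the eligibility section and one screening question. There would be a few more screen failures, and more if crustacean allergy is included. The change screens known sensitivity only; a first reaction in a patient with no history would still have to be handled as an adverse event.

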### Imaging Devices

Radial artery sonographic imaging is required multiple times during the trial and will be performed using either the Versana Active (GE Healthcare, Chicago, Illinois, United States) or EPIC 7 (Phillips Healthcare, Amsterdam, The Netherlands) complex ultrasound systems.

### Patient Data Collection

Collection of patient and procedure data will be performed using a web based electronic case report platform (eCRF).

Demographics that the RAPHE study will be gathering include age, gender, height, weight, and BMI. The accumulated patient history will focus on relevant cardiovascular and other diseases that are known or are assumed to influence hemostasis parameters and thus bleeding of study patients. Collected data will consist of presence of hypertension, presence of dyslipidemia, smoking habits, presence and type (insulin or non-insulin dependent) of diabetes mellitus, prior acute coronary events, prior PCI, prior surgical revascularization, prior stroke, presence of malignancy, presence of liver disease, left ventricular ejection fraction, glomerular filtration rate and thrombocyte count.

Data surrounding the radial puncture itself will also be collected in detail. Overall procedure time, radial artery diameter, any prior punctures, presence of calcium in the radial artery via sonographic evaluation, size of the largest applied introducer sheaths are all recorded.

All relevant times in conjunction with hemostasis device use are detailed and documented. Initial compression of potassium-ferrate and chitosan devices and initial air amount of the pneumatic MCD will be noted, along with the time needed to achieve primary hemostasis. Total time of hemostasis devices will be precisely measured up to the minute in accuracy.

Concomitant medication especially those, influencing puncture site bleeding episodes will all be precisely collected for later assessment. All parenteral and oral anti-coagulant and anti-platelet medication types and utilized doses will also be logged.

### Randomization Procedure

Randomization of consented subjects may only take place in the absence of exclusion criteria after removal of the last coronary catheter, by a physician participating in the study. It will take place in a 1:1:1 ratio, independently for every site via a computer algorithm, between the: pneumatic balloon MCD, potassium-ferrate disc and 100% chitosan sponge devices.

The pneumatic balloon based MCD serving as the control device will be placed on the introducer sheath inflated with the provided syringe to 12 ml-s with simultaneous removal of the introducer. An additional 2 ml-s of air will be inflated in case of acute bleeding and repeated if needed. It will be removed via a simplified patent hemostasis protocol (24), in which, after achieving primary hemostasis, exact titration to true PH we will be achieved by removing 2–3 ml-s of air every 10–15 min using a pulse oximeter to verify patency. At 0 ml-s of remaining air the device will be removed. These procedures will be carried out by qualified nursing staff. Nurses have been instructed to strictly adhere to the PH protocols and to contact study physicians in case of any potential adverse events, especially those in conjunction with radial hemostasis.

The standalone potassium ferrate disc and chitosan sponge devices will both be used in a similar way. They will be placed onto the junction of the intact skin and introducer and manually compressed. To aid better initial compression and prevent device adhesion to bloody surgical gloves, a ball gauze will be placed on the chitosan device. The potassium-ferrate disc will be compressed alone. During compression the introducer will be removed, allowing for a visible amount of blood to appear, which will activate the hemostatic properties in both devices. Strong manual compression will be held for 1 min. Devices will then be banded and held in place using self-adherent wraps as detailed above. Strong, occlusive fixation of the devices will be upheld for a total of 10 min, after which the self-adherent bond will be fully unwrapped until the hemostasis device is visible. By this time both devices will have activated and initiated the coagulation cascade and are firmly attached to the puncture site. If acute bleeding occurs, an additional, minimum 5 minutes of compression will be applied. If initial devices are no longer fit for use, a new similar one will be used. Re-wrapping will then occur without the application of relevant pressure, in a non-occlusive way. During this time the wrapping will only protect the hemostasis device from external influence (e.g., accidental dislodgement, slipping etc.). If the second randomized study device also fails to contain puncture site bleeding a bail-out device of choice shall be applied as per protocol, the choice of which is left to the discretion of the attending physician. After a period of 120 ± 15 min the self-adherent wrapping will be removed. The chitosan sponge device will also be removed using sterile saline irrigation. The potassium-ferrate disc will remain in place and removed by the patient after 24 hours post-procedure.

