## Methods and Analysis

### Study Objectives and Definitions

The objective of the Radial Artery Puncture Hemostasis Evaluation (RAPHE) study is to evaluate the safety and efficacy of two novel, non-compression based, bioactive radial artery hemostasis devices: a 100% chitosan sponge bioactive dressing and the potassium-ferrate based topical discs applied in a standalone configuration. A pneumatic balloon inflatable MCD will serve as a well-established control.

RAPHE is a prospective, randomized, open-label, multicenter clinical trial, with three, high-volume university centers conducting the study, in Europe, Hungary.

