### Statistical Analyses

Data analysis will be done on an intention to treat basis. Baseline patient and disease characteristics will be summarized with detailed descriptive statistics that entail mean, median, SE, SD, IQR and range for continuous variables, while for categorical variables absolute and relative frequencies will be reported. Hypothesis testing of the primary outcome will be done with Fisher’s exact test with a significance level of 95%. Univariate analyses of secondary endpoints will be carried out as superiority analyses with one-way ANOVA, Kruskal-Wallis test, or logistic regressions, depending on the outcome variable type and distribution. Multivariate analyses of secondary endpoints will entail using general or generalized hierarchical mixed effects models depending on variable type and distribution. All statistical analyses will be done in the R statistical environment (21).

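### The primary DOCE test ignores the site strata of the randomisation and plausible baseline predictors; it stays valid but gives up a little precision

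*Protocol article*

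**What the plan says.** - **Sites.** Under Study Objectives and Definitions, the trial is run "with three, high-volume university centers conducting the study".
- **Allocation.** Under Randomization Procedure: "It will take place in a 1:1:1 ratio, independently for every site via a computer algorithm". Site is therefore a stratum of the design. No block method is described. Randomisation happens "after removal of the last coronary catheter, by a physician participating in the study".
- **Primary test.** Under Statistical Analyses: "Hypothesis testing of the primary outcome will be done with Fisher’s exact test with a significance level of 95" per cent. Neither site nor any covariate is mentioned.
- **Adjusted models.** The same section states: "Multivariate analyses of secondary endpoints will entail using general or generalized hierarchical mixed effects models depending on variable type and distribution". No such model is named for the primary outcome.
- **Variables available.** Patient Data Collection lists "radial artery diameter, any prior punctures, presence of calcium in the radial artery via sonographic evaluation, size of the largest applied introducer sheaths", together with history on "diseases that are known or are assumed to influence hemostasis parameters and thus bleeding of study patients". Diameter is measured at the pre-puncture ultrasound, and the largest sheath is settled by the time the last catheter is out. Both are therefore known before allocation.

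**The concern.** When allocation is made within strata and the strata differ in risk, part of the outcome variation lies between strata and is balanced across the arms by design. A pooled two-by-two table still counts that part as noise, so its standard error is slightly too large. Covariates measured before randomisation that predict the outcome offer a similar gain. The plan reserves its multivariable models for secondary endpoints and leaves the main conclusion on the crude table. This is a stated choice, so it does not depend on what an unseen analysis plan might add.

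What is at stake is efficiency only: a few patients' worth of information per arm, or a point or so of power for the non-inferiority claim.

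**Working it through.** **Inputs from the article (Sample Size Calculation):** DOCE 15% in both arms, 80% power, 158 per arm before inflation, 10% drop-out, 200 per arm recruited.

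**Assumptions, because the article does not settle them:** a 10-percentage-point absolute margin and one-sided 5% (see step 1), allocation balanced within site, three sites of equal size, and the site rates and covariate strengths given below.

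**1. Reproduce the plan's figure.** n = (1.645 + 0.842)² × 2 × 0.15 × 0.85 / 0.10² = 157.66, so 158 per arm. This matches exactly, but only with an absolute margin of 10 points and one-sided 5%. One-sided 2.5% gives 201. The margin as worded, 10% relative (1.5 points at 15%), gives 7,007.

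**2. Crude analysis at 200 × 0.9 = 180 evaluable per arm.** SE = √(2 × 0.1275 / 180) = 0.0376. Then 0.10 / SE = 2.657, and power = Φ(2.657 − 1.645) = 84.4%. At one-sided 2.5% it is 75.7%.

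**3. Stratify by site.** Variance ratio = mean of p(1 − p) over sites, divided by 0.15 × 0.85 = 0.1275. Power = Φ(2.657 / √ratio − 1.645).

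| Assumed site rates | Mean p(1 − p) | Ratio | Variance saved | Power (crude 84.4%) |
|---|---|---|---|---|
| 13/15/17% | 0.1272 | 0.998 | 0.2% | 84.5% |
| 10/15/20% | 0.1258 | 0.987 | 1.3% | 84.8% |
| 5/15/25% | 0.1208 | 0.948 | 5.2% | 86.1% |

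At one-sided 2.5%, the last row goes from 75.7% to 77.9%.

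**4. Check by simulation** (3 sites × 60 per arm, Wald non-inferiority tests, 10-point margin).
- Power, crude to stratified: 84.6% to 85.1% at 10/15/20%, and 85.0% to 86.3% at 5/15/25%.
- With equal site rates it still rises from 84.4% to 84.7%, where there is nothing to gain. About 0.3 of a point in each comparison therefore comes from the simple stratified Wald variance being slightly too small (its type I error was about 5.2%).
- One-sided type I error of the crude test: 5.0% at 10/15/20% and 4.75% at 5/15/25%. The crude test is valid and, if anything, slightly conservative.

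**5. Add covariates.** Suppose the baseline covariates together form a risk score with AUC of about 0.64, 0.69 or 0.75. Standardisation from a logistic model then cut the variance of the risk difference by 2.6%, 6.6% and 11.2% in simulation. In patients, this is from 157.66 × 0.026 ≈ 4 to 157.66 × 0.112 ≈ 18 per arm. For power at 180 per arm, a 5% saving gives 86.0% and a 10% saving gives 87.6%, against 84.4%. Site was not in this simulation, so adding these savings to those in step 3 is an approximation.

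**6. Dependence on the margin.** With a 1.5-point margin, power at 200 per arm is about 11%, and about 12% even if 20% of the variance were explained. Adjustment matters only if the 10-point reading is the intended one.

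**The case against.** An unadjusted primary test is a legitimate choice, and with balanced allocation it favours no wrong conclusion. The gain depends wholly on assumed site rates: the article gives none, and only a fivefold spread between sites brings it near 2 power points. All of this stands, and it limits the point to an optional improvement.

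Several stronger readings are tempting, but the article does not support them:

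- **That these sites must differ widely, because radial occlusion is quoted at under 1% to 33%.** That range is literature-wide. Sample Size Calculation calls 33% unreasonable for the participating centres, and occlusion is only one of three DOCE components.
- **That strong predictors are being ignored.** No association with DOCE is quantified. The history items are described as known or assumed to matter, and excluding arteries below 1.8 mm narrows the range of diameter.
- **That the planned confidence interval is too wide.** Statistical Analyses states no interval. The remark applies only to a crude interval, should one be used for the non-inferiority claim.
- **That three sites are too few for the hierarchical models.** The article does not say what the hierarchical level is, so this would be a guess.
- **That the pooled standard error is certainly overstated.** This needs allocation balanced within site. The article states separate randomisation by site but names no blocks.

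**Conclusion.** The point holds as a small efficiency matter. The design stratifies by site, the named primary test uses neither site nor any covariate, and usable pre-randomisation variables are collected. Site stratification is worth about 0 to 2 power points. Plausible covariates might save a further 3 to 11% of variance, or roughly 4 to 18 patients per arm out of 158. These figures rest on the assumptions set out above, chiefly the 10-point absolute margin and the invented site rates and covariate strengths; the article offers nothing to narrow them.

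A reader should not infer that the crude comparison is invalid or biased. The point ranks below two larger problems in the same sections: the relative margin as worded does not yield 158 per arm, and Fisher's exact test as stated tests equality, whereas the hypothesis is non-inferiority. Covariate adjustment repairs neither.

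**What to change.** The primary analysis needs rewording in any case so that it tests non-inferiority, and the site strata can be built in at the same time.

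1. **Primary.** For each bioactive device versus the pneumatic control, estimate the site-stratified DOCE risk difference with Mantel-Haenszel weights. Compare its stratified confidence interval with the non-inferiority margin. A stratified score interval (Miettinen-Nurminen) is a suitable form and avoids relying on the simple Wald variance seen in the simulation.
2. **Supportive, pre-specified.** Report the standardised risk difference from a logistic model with treatment, site, sheath size and radial artery diameter. Keep the list this short: at 15% there are only about 27 events per arm with 180 evaluable patients (0.15 × 180) and 30 with 200 (0.15 × 200).

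The cost is wording in the analysis section. No new data are needed, and the sample size need not change on this account.
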